   1. OTHER PARAMETERS

**DEMOGRAPHY AND BASELINE**

**Collected variables**

- Randomization group: categorical variable. Intervention or control group.
- Stratification group: categorical variable. COPD or Chronic heart failure or Other
- Time of inclusion: date variable. Expressed as date (DD/MM/YYYY) and hour (HH:MM)
- Sex: categorical variable. Male or female
- Age: continuous variable. Expressed in years
- Height: continuous variable. Expressed in years, rounded to the nearest integer
- Weight: continuous variable. Expressed in kilos, with a precision of 0.5.
- Body mass index: continuous variable. Expressed in kilos, rounded to the nearest integer
- Hospital admission date: date variable. Expressed as date (DD/MM/YYYY). In case of referral from another hospital, hospital admission date is the date of admission in the previous hospital.
- ICU admission date: date variable. Expressed as date (DD/MM/YYYY). In case of referral from another ICU, ICU admission date is the date of admission in the previous ICU.
- Intubation date: date variable. Expressed as date (DD/MM/YYYY). In case of multiple intubation during ICU stay, the date corresponds the most recent intubation.
- Intubation due to respiratory failure: categorical variable (yes or no)
- Intubation due to hemodynamic failure: categorical variable (yes or no)
- Intubation due to neurological failure: categorical variable (yes or no)
- Intubation due to major surgery: categorical variable (yes or no)
- Intubation due to other reason: categorical variable (yes or no)
- Admission context: categorical variable (medical, planned surgery, emergent surgery, trauma)
- SAPSII score: continuous variable, ranging from 0 to 163
- Respiratory SOFA score, discrete variable, ranging from 0 to 4
- Hemodynamic SOFA score, discrete variable, ranging from 0 to 4
- Hepatic SOFA score, discrete variable, ranging from 0 to 4
- Renal SOFA score, discrete variable, ranging from 0 to 4
- Neurological SOFA score, discrete variable, ranging from 0 to 4
- Hematologic SOFA score, discrete variable, ranging from 0 to 4
- COPD status: categorical variable. None or suspected or proven
- Gold stage: categorical variable. Stage 1, 2,3 or 4. Only for COPD patients.
- Chronic respiratory failure: categorical variable (yes or no)
- Chronic respiratory failure type: categorical variable (obstructive, restrictive or mixed). Only for chronic respiratory failure patients.
- Chronic respiratory support: categorical variable (oxygen, NIV, both or none). Only for chronic respiratory failure patients.
- Chronic heart failure: categorical variable (yes or no)
- Charlson score: continuous variable, ranging from 0 to 43
- Baseline ventilator parameters:
  - Ventilation mode: categorical variable. Pressure support, volume controlled or other
  - Minute ventilation: continuous variable. Expressed in liters/min, with a precision of 0.1
  - Respiratory rate: continuous variable. Expressed in /min, as an integer
  - PEEP: continuous variable. Expressed in cmH2O, as an integer
  - FiO2: continuous variable. Expressed in %, as an integer
- Baseline arterial blood gas:
  - pH: continuous variable. Expressed without unit, with a precision of 0.01
  - PaCO2: continuous variable. Expressed in mmHg, as an integer
  - PaO2: continuous variable. Expressed in mmHg, as an integer
  - Bicarbonates: continuous variable. Expressed in mmol/L, as an integer
  - Base excess: continuous variable. Expressed in mmol/L, as an integer
  - Lactate: continuous variable. Expressed in mmol/L, as an integer

**Computed variables**

- Hospital length of stay at inclusion: continuous variable. Expressed in days, equal to day of inclusion minus day of hospital admission
- ICU length of stay at inclusion: continuous variable. Expressed in days, equal to day of inclusion minus day of ICU admission
- Intubation duration at inclusion: continuous variable. Expressed in days, equal to day of inclusion minus day of intubation
- Total SOFA score, computed as the sum of the respiratory, hemodynamic, hepatic, renal, neurological and hematologic SOFA, discrete variable, ranging from 0 to 24

**PROTOCOL VIOLATIONS**

Five protocol violations will be assessed, categorical variable (yes or no):

- 1. Patients not extubated despite the presence of both weaning and extubability criteria
  2. Patients extubated despite lack of weaning or extubability criteria
  3. Post-extubation NIV performed despite not required per protocol
  4. Rescue NIV for post-extubation respiratory distress (except for WIPO or hypercapnic failure for COPD/chronic respiratory failure patients)
  5. Post-extubation NIV not done despite required per protocol

**DAILY ASSESSMENTS**

These variables will be collected from Day 1 until Day 90:

- If the patient is intubated (SBT data):
  - Preliminary weaning criteria: categorical variable. Present or absent.
  - SBT result: categorical variable. Success or failure.
  - Arterial blood gas in case of SBT success:
    - pH: continuous variable. Expressed without unit, with a precision of 0.01
    - PaCO2: continuous variable. Expressed in mmHg, as an integer
    - PaO2: continuous variable. Expressed in mmHg, as an integer
    - FiO2: continuous variable. Expressed in %, as an integer. For control group, FiO2 is equal to 21+ 3*O2 flow on T-piece
  - Cough score: categorical variable. 0, 1, 2, 3, 4, 5
  - Abundance of respiratory secretions: categorical variable. 0, 1, 2, 3, 4
  - For intervention group: result of SBT-TP, categorical variable. Success or failure.
  - Summary of extubability criteria
    - Acceptable cough (cough score ≥3): categorical variable. Yes or No
    - Acceptable respiratory secretions (abundance of respiratory secretions ≤2): categorical variable. Yes or No
    - No general anaesthesia planned on the next 24h: categorical variable. Yes or No
    - No argument for laryngeal obstruction: categorical variable. Yes or No
    - Number of positive extubability criteria: numerical variable. Ranging from 0 to 4
  - Date (JJ/MM/AAAA)
  - Hour of extubation (HH:MM)
- If the patient is extubated (extubation data):
  - Patient extubated today: categorical variable. Yes or no
  - Extubation type: categorical variable. Programmed extubation per protocol; programmed extubation (protocol violation) or auto-extubation
  - Post-extubation prophylactic NIV (on the day of extubation and the following day): categorical variable. Yes or no
    - In case post-extubation prophylactic NIV:
      - Per-protocol: categorical variable. Yes or no
        - If per protocol, reason(s) for NIV

SBT-TP failure (for intervention group): categorical variable. Yes or no

Age>65 years old: categorical variable. Yes or no

COPD: categorical variable. Yes or no

Chronic heart failure: categorical variable. Yes or no

Chronic respiratory failure: categorical variable. Yes or no

PaCO2>45mmHg at the end of SBT: categorical variable. Yes or no

- - - - - Duration of NIV: continuous variable. Expressed in hours, as an integer
    - In case of no prophylactic NIV:
      - Reason: categorical variable. Per protocol, violation of protocol or contra-indication
  - Post-extubation rescue NIV (during the 7 days following extubation): categorical variable. No, per protocol, protocol violation
  - Post-extubation high-flow nasal oxygen (during the 7 days following extubation): categorical variable. No, Yes
  - Respiratory physiotherapy (during the 7 days following extubation): categorical variable. No, manual therapy, instrumental therapy
- Reintubation (reintubation data): categorical variable. Yes or no
  - Reintubation criteria: categorical variable. Neurological, Hemodynamic, other, Respiratory
  - In case of respiratory criteria reintubation, aetiology: categorical variable:
    - Respiratory exhaustion: Yes or no
    - Abundant respiratory secretion: Yes or no
    - Pneumonia: Yes or no
    - Cardiac pulmonary edema: yes or no
    - Laryngeal dyspnea: yes or no
  - Reintubation for general anaesthesia lasting less than 24h: categorical variable. Yes or no
- Status at the end of the day:
  - Respiratory status: categorical variable: yes or no
  - Weaning protocol: categorical variable: pursuit or end
  - Weight: continuous variable. Expressed in kg, with a precision of 0.5

**TERTIARY OUTCOMES**

- Tracheostomy during ICU stay: categorical variable: Yes or no
  - Time of tracheostomy: date variable. Expressed as date (DD/MM/YYYY) and hour (HH:MM)
  - Method of tracheostomy: categorical variable. Percutaneous or surgical
  - Indication(s) for tracheostomy: categorical variable:
    - Difficult weaning: yes or no
    - Swallowing disorder/abundant bronchial secretions: yes or no
    - Other: yes or no
  - Patient successfully weaned from ventilation: yes or no
    - If yes: Time of successful weaning: date variable. Expressed as date (DD/MM/YYYY) and hour (HH:MM)
- End of protocol: categorical variable. Secondary exclusion or end of protocol
  - Date of study end: date variable. Expressed as date (DD/MM/YYYY)
  - In case of secondary exclusion: categorical variable. Transfer to another ICU not participating to the study; Consent withdrawal; In case of serious adverse event, according to the clinician in charge.
  - In case of end of protocol (Cause of end of protocol): categorical variable. No reintubation in the 7 days following extubation; Withdrawing of care or withholding of reintubation decision; ICU discharge ; death ; patient still intubated at Day 90.
- Severe adverse event: categorical variable. Yes or no.
- Respiratory status at ICU discharge (Day 28, Day 90): categorical variable. Not ventilated, non-invasive ventilation (except CPAP), invasive ventilation (tracheostomy), invasive ventilation (intubated), tracheostomy (without ventilation), dead, lost to follow up
- Date of ICU discharge: date variable. Expressed as date (DD/MM/YYYY)
- Date of hospital discharge: date variable. Expressed as date (DD/MM/YYYY)
- Successful extubation: categorical variable. Yes, death or weaning failure
- Successful extubation rank. Discrete variable. NA in case of death
- Time of successful extubation: date variable. Expressed as date (DD/MM/YYYY) and hour (HH:MM).
- Number of reintubation: Discrete variable

1. Statistical Methodology
   1. GENERAL METHODOLOGY

Quantitative variables will be will be described using the following statistics: number of missing data, mean, standard deviation, quartiles, minimum and maximum values, number and rate of missing variables, and compared between groups with the Mann-Whitney test. No normality check will be performed. Qualitative variables will be reported as absolute and relative frequencies, number and rate of missing variables, and compared between groups with the chi-2 test or the Fisher exact test. Variables will be compared between both groups, except for specific analysis described in 5.2. We will not adjust p-value for multiple comparison. Univariable absolute difference will be reported for each variable as difference [95% confidence interval]. The Hodges-Lehmann method will be used to compute unbiased median differences for outcomes and their CI95%. For qualitative variables, 95% confidence interval will be computed through bootstrapping.

P-value <0,05 with a bilateral hypothesis will be considered as significant. All the analyses will be carried out using R for Windows.

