   1. STUDY DESIGN

- The study is a monocentric prospective open labelled, randomized controlled superiority trial, with two parallel groups and balanced randomization stratified into 3 groups (according to patients prior diseases), with a 1:1 ratio, using random blocks of size 4, 6 and 8.
- Type of control : alternative strategy
- Level and method of blinding : none (open labelled study)
- Method of treatment assignment: randomization with stratification
- Number of subject : 94 patients (47 per group)
- Duration of study : 90 days

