  1. TREATMENT GROUPS

In this study, two strategies of weaning are compared: “assisted strategy” (intervention group) and “unassisted strategy” (control group).

Allocation sequence will be computer generated with stratification into 3 groups:

- Patients with chronic heart failure (CHF) (defined by an ejection fraction <45%)

- Patient with COPD or chronic respiratory failure

- Other patients

Randomization was done in each stratum with random blocks of size 4, 6 and 8.

Allocation sequence was concealed in a sealed opaque envelope with sequential number in each stratum. Allocation sequence was generated by a person independent from the investigator and not enrolling nor assigning patients to intervention.

Clinicians and investigators are enrolling patients and assigning patients to intervention according to the allocation.

Due to the type of intervention, no blinding is possible for the clinicians and the patients. During the database cleaning process, the statistician will be blind of the treatment allocation.

Patients are secondary excluded of the study if:

- Patient is transferred to another ICU
- Consent withdrawal
- Severe adverse event due to the study (on clinician decision)

These patients will be replaced.

- 1. STUDY POPULATION

Inclusion criteria:

• Patient 18 years old or more

• Intubated and ventilated in intensive care unit for more than 24 hours

• Patient ready for weaning evaluation

• Failure of a first SBT-TP

Exclusion criteria:

• Chronic neuromuscular disease

• Guillain-Barré Syndrome

• Central nervous system disease with consciousness disorder (i.e inability to obey a simple command)

• Tracheostomy

• Chronic disease with life expectancy less than 1 year

• Pregnancy, breast feeding

• Withholding life support regarding a reintubation

• Prisoner or patient interned in psychiatric hospital

• Under legal protective measures

• Language barrier

• Lack of social security

• Lack of the patient's consent (or of the next of kin where appropriate)

• Patient under an exclusion period after enrolment in another research study

- 1. INTERVENTION

The interventions will be started within the 6hr following inclusion.

Intervention group (assisted weaning strategy)

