  1. PRIMARY DATA ANALYSES

5.2.1 Outcome variables

5.2.1.1 Primary outcome

Primary outcome (time to successful extubation) is subjected to competitive risk (death). However, assuming competing risk will be identical in both groups, survival analysis will be done according to a cause-specific analysis (Cox model) with randomization strata as covariate. Hence, primary outcome will be assessed with the Hazard Ratio (HR) produced by Cox model.

Time to event will be:

- For patients successfully extubated: time from inclusion to successful extubation
- For patients who died before successful extubation or Day 90: time from inclusion to death, with censoring at this time point
- For patients not weaned from mechanical ventilation at Day 90 will be censored at this time point.

Two diagnosis will be performed:

1. Proportional hazard assumption will be checked through scaled Schoenfeld residuals statistical test and graphical plot
2. Verification of influential observations: outliers will be identified by 1) plotting deviance residuals and checking symmetrical distribution around zero and 2) plotting the estimated changes in the regression coefficients upon deleting each observation in turn (dfbeta) . In case of influential observation, the observation will be checked for error, corrected if wrong, or conserved if true.

If the proportional hazard assumption is not met, a chronological variable will be used, if possible, otherwise, a log-rank test will be performed.

To account for competing risk, a sensitivity analysis will be performed on the main outcome as follows: the main outcome will be described with cumulative incidence functions and analyzed with a Fine and Gray model with successful extubation as event and death as competitive risk, with randomization strata as covariate. Proportional hazard assumption will be checked by plotting Schoenfeld residuals against event time for each covariate. If the proportional hazard assumption is not met, a chronological variable will be used, if possible.

We will provide graphical representation using a Kaplan Meier curve for the Cox model, depicting the two groups without stratification and a cumulative incidence graph for Fine and Gray model depicting the two groups without stratification, with successful extubation and death as events.

Results will be reported a table with four columns (intervention group, control group, Hazard ratio, p-value). The subgroup analysis will be presented as a forest plot.

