5.2.1.2 Secondary outcomes

Analysis will be carried out as described in 5.1. Results will be reported a table with four columns (intervention group, control group, univariable absolute difference with 95% confidence interval, p-value).

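### Secondary outcomes are compared without the randomisation strata that the primary models include; if the strata are prognostic, these comparisons are modestly conservative

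*Protocol*

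**What the plan says.** Protocol section 2.1 describes a design "with two parallel groups and balanced randomization stratified into 3 groups (according to patients prior diseases), with a 1:1 ratio". Section 2.2 names the three strata and adds "Randomization was done in each stratum with random blocks of size 4, 6 and 8".

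For the primary outcome, section 5.2.1.1 carries the strata into the model: "survival analysis will be done according to a cause-specific analysis (Cox model) with randomization strata as covariate". The Fine and Gray sensitivity model has the same covariate.

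For the secondary outcomes, section 5.2.1.2 says only "Analysis will be carried out as described in 5.1", with results tabulated as "univariable absolute difference with 95% confidence interval, p-value". Section 5.1 fixes the methods. Quantitative variables are "compared between groups with the Mann-Whitney test" and qualitative variables are "compared between groups with the chi-2 test or the Fisher exact test". The effect measure follows: "Univariable absolute difference will be reported for each variable as difference [95% confidence interval". Intervals come from the Hodges-Lehmann method for quantitative outcomes and from bootstrapping for qualitative ones, and strata are mentioned for neither. Section 5.1 makes an exception for specific analyses set out in 5.2, but it does not help here because 5.2.1.2 refers straight back to 5.1.

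**The concern.** Blocking within strata keeps the arms nearly balanced on the stratification factor, so differences between strata contribute little to the comparison of arms. An unstratified test or interval still counts those differences as random error. If the strata are prognostic, the standard error is overstated: the true type I error falls below 5%, intervals are wider than the design warrants, and power is lost.

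With 47 patients per arm there is little precision to spare. Conservatism is also not always the safe direction. Secondary objective 8 asks whether the intervention leads to more reintubation, and objective 7 concerns mortality. For a possible harm, a conservative test makes a signal easier to miss.

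**Working it through.** **The plan's own figure.** Section 2.5 gives a two-sided alpha of 5%, power of 80% and a hazard ratio of 2. Schoenfeld's formula gives 4 × (1.960 + 0.842)² / (ln 2)² = 4 × 7.849 / 0.4805 = 65.3, so 66 events as stated. Then 66 / (1 − 0.30) = 94.3, stated as 94. Power with 66 events is 80.4%. The figure reproduces and does not depend on this point. The protocol gives no power or precision figure for secondary outcomes.

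**Approximate size by formula.** Let R² be the share of outcome variance explained by the strata. The unstratified standard error uses the total variance, while under stratified blocks the difference varies with only about (1 − R²) of it. So:

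- width of adjusted interval / width of unadjusted interval ≈ √(1 − R²)
- true two-sided type I error of the unadjusted test ≈ 2 × [1 − Φ(1.96 / √(1 − R²))]

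For R² = 0.10 this gives a width ratio of 0.949 and an error of 2 × [1 − Φ(2.066)] = 3.9%. For R² = 0.20 it gives 0.894 and 2 × [1 − Φ(2.191)] = 2.8%.

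**Simulation, continuous outcomes.**
- From the protocol: N = 94, three strata, 1:1 allocation, random blocks of 4, 6 and 8 in each stratum.
- Assumed: stratum shares 20/30/50%, normal outcomes, a treatment effect of 0.6 total SD, and the R² values shown.
- 3000 runs per scenario. The Monte Carlo standard error is about √(0.05 × 0.95 / 3000) = 0.4 points near 5% and √(0.8 × 0.2 / 3000) = 0.7 points near 80%.
- Width is that of the normal-theory mean difference, used as a proxy for the planned Hodges-Lehmann interval.

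| R² | Adjusted / unadjusted width | Type I error, Mann-Whitney vs van Elteren | Power, Mann-Whitney vs van Elteren |
|---|---|---|---|
| 0 | 1.00 | 5.5% vs 5.4% | 78.9% vs 78.6% |
| 0.05 | 0.98 | 4.1% vs 4.8% | 80.7% vs 81.6% |
| 0.10 | 0.95 | 4.1% vs 5.1% | 80.3% vs 82.4% |
| 0.20 | 0.89 | 3.1% vs 5.8% | 81.6% vs 87.2% |
| 0.30 | 0.84 | 2.0% vs 5.4% | 84.1% vs 91.5% |

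The width ratios and the Mann-Whitney error rates agree with the formulas.

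**Second simulation, other assumptions.** Here the shares are 25/25/50%, and both disease strata are shifted by d within-stratum SD from the third. The strata then explain (d²/4) / (1 + d²/4) of the variance.

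| d | Variance explained | Type I error, Mann-Whitney vs van Elteren | Power, Mann-Whitney vs van Elteren |
|---|---|---|---|
| 0 | 0% | 5.2% vs 5.2% | 80% vs 80% |
| 0.5 | 0.0625/1.0625 = 6% | 4.3% vs 5.3% | 78% vs 79% |
| 0.8 | 0.16/1.16 = 14% | 3.4% vs 5.2% | 75% vs 79% |
| 1.0 | 0.25/1.25 = 20% | 2.9% vs 5.2% | 73% vs 80% |

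The gap between the two tests is of the same order in both simulations.

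**Simulation, binary outcomes.** Assumed odds ratio 0.3, shares 20/30/50%. Power of chi-2 vs Cochran-Mantel-Haenszel:

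- equal stratum rates of 30%: 62.0% vs 61.2%
- rates 40/35/23%: 61.2% vs 61.4%
- rates 55/40/14%: 54.4% vs 58.0%

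**The case against.** The loss depends wholly on how strongly the strata predict each secondary outcome, and the protocol gives no figure for that. A reader might infer that the strata were chosen because they predict weaning. The text does not say so: section 2.1 speaks only of prior diseases and section 2.2 lists the groups without a rationale. It is likewise tempting to state the wide intervals and lost power as fact, but with no stratum effect nothing is lost. This objection stands, so the point must be conditional. Prognostic strata remain plausible for some outcomes. Under section 2.4, heart failure, chronic respiratory failure and COPD are each criteria for prophylactic NIV in both arms, and secondary outcome 3 runs to NIV cessation in patients who receive it.

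A reader might also take the plan to be invalid. It is not: the unadjusted difference is unbiased and type I error is not inflated. Nor do the two approaches contradict each other. The plan openly labels the secondary effect as univariable, and a crude absolute difference and a strata-adjusted hazard ratio are different summaries.

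Two limits on the evidence also stand. The width figures use a normal-theory proxy, not the planned Hodges-Lehmann or bootstrap intervals. The shift model also does not represent ventilator-free days, which are set to 0 for deaths and prolonged ventilation.

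The objection does not supply a reason to drop the strata. The protocol fixes an unstratified method explicitly and does not explain why it departs from the primary models.

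**Conclusion.** The point holds as a matter of efficiency and calibration in the secondary analyses, conditional on the strata being prognostic. For continuous outcomes the loss ranges from nil to about 7 power points and 16% of interval width as the variance explained goes from 0 to 30%. At the modest values of 5 to 10% it is about 1 to 2 points and 2 to 5%. For binary outcomes it is 0 to about 4 points, and the upper end needs sharply different stratum rates. Stratum shares, stratum effects and treatment effects are all assumptions. This is a low-cost improvement and does not correct an error that would invalidate a result.

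**What to change.** In sections 5.1 and 5.2.1.2, make the main comparison of secondary outcomes stratified by randomisation stratum:

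- **Quantitative outcomes:** van Elteren test, with a stratum-aligned Hodges-Lehmann difference and its 95% interval.
- **Binary outcomes:** Cochran-Mantel-Haenszel test, with a stratum-weighted risk difference and a bootstrap interval resampled within strata.
- **Univariable results:** keep them as supplementary.

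No wording is needed for time-to-event secondary analyses, because section 5.1 names no survival method for the change to act on.

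The cost is a change of wording and a few lines of R. Stratification group is already a collected variable (section 4.3), and the sample size does not change. If the strata are not prognostic, the simulated loss from stratifying is at most about one power point (78.9% to 78.6% for continuous outcomes, 62.0% to 61.2% for binary). The change should be fixed before outcomes are compared by arm.

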In a pilot observational study on 88 patients, median time between first SBT and extubation was 22h with a strategy using SBT-PS and PEEP. We hypothesized that a between-arm difference of at least 24 hours would be clinically relevant to prefer a SBT strategy over one another. With an alpha risk of 5% and a bilateral hypothesis, a power of 80% and a hazard ratio of 2 (based on the ratio of median duration of time between first SBT and successful extubation), a total of 66 successful extubation would be needed. Accounting for both potential deaths before successful weaning and weaning failure (assumed to amount to 30%), we plan to include 94 patients (47 per group).

- 1. STUDY PROCEDURE

|  | Inclusion (day-1) | Day-2 to day-90 | ICU discharge / Death | Day-28 | Day-90 |
| --- | --- | --- | --- | --- | --- |
| Demographic data | X |  |  |  |  |
| Patient weaning readiness | X | X* |  |  |  |
| SBT result | X | X* |  |  |  |
| Arterial blood gas | X | X* |  |  |  |
| *If SBT success* |  |  |  |  |  |
| Cough score | X | X* |  |  |  |
| Abundancy of respiratory secretions | X | X* |  |  |  |
| Extubability criteria | X | X* |  |  |  |
| *If extubation* |  |  |  |  |  |
| Extubation date and time | X** | X** |  |  |  |
| Extubation type (protocolized/self-extubation) | X** | X** |  |  |  |
| Post-extubation NIV characteristics | X** | X** |  |  |  |
| Respiratory physiotherapy characteristics | X*** | X*** |  |  |  |
| High-flow nasal oxygen use | X | X*** |  |  |  |
| Invasive mechanical ventilation status | X | X*** |  |  |  |
| *If reintubation* |  |  |  |  |  |
| Reintubation criteria | X | X |  |  |  |
| *If tracheostomy performed* |  |  |  |  |  |
| Characteristics of tracheostomy |  |  | X |  |  |
| *Follow-up data* |  |  |  |  |  |
| Date/hour of cessation of invasive ventilation and NIV |  |  | X |  |  |
| End of study |  |  |  |  |  |
| Respiratory status |  |  | X | X | X |
| Mortality |  |  | X | X | X |
| *As long as the patient is intubated or tracheostomized  **On the day of extubation and the day after  ***during the 7 days following extubation  NIV denotes non-invasive ventilation, and SBT spontaneous breathing trial. | | | | | |

1. Population of Analysis (intention to treat population)

All subjects who were randomized except patients secondary excluded from the study due to:

- Transfer to another ICU not participating to the study
- Consent withdrawal
- Lack of inclusion criteria or presence of exclusion criteria

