   1. PRIMARY OUTCOME

The primary outcome will be duration (in hours) between study inclusion and successful extubation (defined by the absence of reintubation or death within the 7 days (168 hours) following extubation). Reintubation and resuming of mechanical ventilation for less than 24h related to unplanned surgical procedure will not be considered as extubation failure. Patients extubated but exiting ICU within the 7 days following extubation will be considered as successful extubation. In patients not meeting extubation success criteria, data will be censored at day-90 or date of death whichever comes first.

- 1. SECONDARY PARAMETERS OUTCOMES

1. Rate of first successful extubation: number of patients successfully extubated after their first extubation/total number of patients per group
2. Invasive mechanical ventilation duration (expressed in hours): total cumulative time spent on invasive mechanical ventilation since inclusion per group. Each time period spent on invasive mechanical ventilation from inclusion until successful extubation are summed up. Patients not experiencing successful extubation will be censored at Day 90 or time of death (if earlier than Day 90).
3. Mechanical (invasive and non-invasive) ventilation duration (expressed in hours): total cumulative time spent on invasive and non-invasive mechanical ventilation since inclusion per group.
   - If the patient is successfully extubated with post-extubation NIV: date/time of NIV cessation minus date/time of inclusion. (or date/time of ICU discharge If NIV not ceased at ICU discharge)
   - If the patient is successfully extubated without post-extubation NIV: date/time of successful extubation minus date/time of inclusion.
   - Patients not experiencing successful extubation will be censored at Day 90 or time of death (if earlier than Day 90).
4. Ventilator-free days (VFD) at Day-28 and Day-90. VFD will be computed as follows from the day of inclusion:
   - VFD = 0 if the patient dies between inclusion and day-28 for VFD at day-28, or if the patient dies between inclusion and day-90 for VFD at day-90

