   - VFD = 28-x for VFD at day-28 or VFD = 90-x for VFD at day-90 if the patient is successfully weaned from invasive mechanical ventilation, with x being the number of days from inclusion to last successful extubation. Successful weaning from mechanical ventilation will be defined as extubation without reintubation within at least 7 days (or weaning from mechanical ventilation for at least 7 days for patients with tracheostomy)
   - VFD = 0 if the patient is mechanically ventilated for more than 28 days after inclusion for VFD at day-28, or more than 90 days after inclusion for VFD at day-90
5. ICU stay (days): ICU length of stay between inclusion and ICU discharge
6. Hospital stay (days): hospital length of stay between inclusion and hospital discharge (to home or rehabilitation facility).
7. ICU, day-28, and day-90 mortality: defined as the ratio of the number of death over each period over the total number of patients per group.
8. Reintubation rate: number of patients with any reintubation divided by the number of patients per group

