5.2.5 Tertiary outcomes

Analysis will be carried out as described in 5.1.

Tracheostomy data will be reported a table with four columns (overall population, intervention group, control group, p-value) or in text if N<5.

We will report the following tertiary outcomes in a table with four columns (intervention group, control group, univariable absolute difference with 95% confidence interval, p-value):

- - Cause of end of protocol No reintubation in the 7 days following extubation; Withdrawing of care or withholding of reintubation decision; ICU discharge; death; patient still intubated at Day 90.
- Severe adverse event
- Respiratory status at ICU discharge (Day 28, Day 90)
- Successful extubation status
- Successful extubation rank
- Number of reintubation

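### The Hodges-Lehmann difference set for all outcomes in Section 5.1 does not suit zero-heavy ones: it returns 0 [0; 0] for number of reintubations and responds weakly to a change in the share of zero ventilator-free days

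*Protocol*

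**What the plan says.** Section 5.1 compares quantitative variables with the Mann-Whitney test and fixes the effect measure in one sentence: "The Hodges-Lehmann method will be used to compute unbiased median differences for outcomes and their CI95". No class of outcome is exempted. Section 5.2.1.2 sends the secondary outcomes to 5.1 and asks for a column with the absolute difference and its 95% CI next to the p-value. Section 5.2.5 does the same for the tertiary list: "We will report the following tertiary outcomes in a table with four columns", the third and fourth being the difference with its CI and the p-value.

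Two kinds of outcome covered by this rule have a large mass at zero.

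- VFD at day 28 and day 90 (Section 4.2, item 4). Death scores zero ("VFD = 0 if the patient dies between inclusion and day-28 for VFD at day-28"), and so does prolonged ventilation ("VFD = 0 if the patient is mechanically ventilated for more than 28 days after inclusion for VFD at day-28"). Day 90 has parallel rules.
- Number of reintubations (Section 4.3): "Number of reintubation: Discrete variable". It is in the Section 5.2.5 list.

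**The concern.** The Hodges-Lehmann estimate is the median of all between-group pairwise differences. It estimates a single shift, and so a difference in medians, when one distribution is the other moved along the scale. An outcome with a point mass at zero cannot behave that way, because an effect on the share of zeros is not a shift.

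Two consequences follow. When more than half of the pairs are tied, the estimate is exactly zero whatever the remaining pairs show, and the rank-based interval can collapse onto zero as well. When the effect lies mainly in how many patients score zero, the estimate moves little. At stake is whether the effect column can be read together with the p-value beside it, for one tertiary count and one secondary outcome assessed at two time points.

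**Working it through.** **Inputs from the protocol (Section 2.5).** 47 patients per group; 30% deaths and weaning failures, not split by group; pilot median 22 h and a relevant difference of 24 h, hence 22 v 46 h. The protocol states no Hodges-Lehmann figure. Its own arithmetic reproduces: with "a power of 80% and a hazard ratio of 2", Schoenfeld's formula gives 4 × (1.960 + 0.842)² / (ln 2)² = 65.3, matching "a total of 66 successful extubation would be needed"; 66 / 0.70 = 94.3, against the planned 94.

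**Assumed.** Reintubation rates, the split of VFD zeros by group, and exponential extubation times.

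**1. Number of reintubations.** There are 47 × 47 = 2,209 pairs. The rank-based 95% limits lie at about position 2,209/2 ∓ 1.96 × √(2,209 × 95 / 12) = 1,104.5 ∓ 259.2, that is, about the 845th smallest and 845th largest difference.

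Take 5 v 14 patients reintubated once each:
- difference −1: 42 × 14 = 588 pairs
- difference 0: 42 × 33 + 5 × 14 = 1,456 pairs
- difference +1: 5 × 33 = 165 pairs

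Ordered positions 589 to 2,044 are all zero, so the estimate and both limits are zero. In general the lower limit leaves zero only when the −1 pairs reach about 845.

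| Reintubated, of 47 | −1 pairs | Hodges-Lehmann [95% CI] | Mann-Whitney p | Mean difference |
|---|---|---|---|---|
| 5 v 12 | 504 | 0 [0; 0] | 0.063 | −0.15 |
| 5 v 14 | 588 | 0 [0; 0] | 0.022 | −0.19 |
| 5 v 16 | 672 | 0 [0; 0] | 0.007 | −0.23 |
| 7 v 19 | 760 | 0 [0; 0] | 0.006 | −0.26 |
| 12 v 24 | 840 | 0 [0; 0] | 0.011 | −0.26 |
| 5 v 21 | 882 | 0 [−1; 0] | 0.0002 | −0.34 |

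The result is symmetric if the groups are exchanged. For the cases run in R, the Wilcoxon routine gave estimates within 0.0001 of zero.

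**2. VFD.** An exponential time with median m hours, counted in whole days, has mean 1 / (2^(24/m) − 1): 0.89 days for 22 h and 2.30 days for 46 h. The expected VFD is (1 − share of zeros) × (horizon − that mean).

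- VFD-28, zeros 20% v 40%: 0.8 × 27.11 − 0.6 × 25.70 = 6.3 days.
- VFD-90, zeros 20% v 40%: 0.8 × 89.11 − 0.6 × 87.70 = 18.7 days.
- Either horizon, zeros 30% in both: 0.7 × (2.30 − 0.89) = 1.0 day.

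Simulated trials with 47 per group gave these typical (median) Hodges-Lehmann estimates:

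| Zeros, assisted v control | Mean gain, VFD-28 | Mean gain, VFD-90 | Hodges-Lehmann, either horizon |
|---|---|---|---|
| 20% v 40% | about 6 | about 19 | about 2 |
| 25% v 35% | about 3.5 | about 10 | about 1 |
| 30% v 30% | about 1 | about 1 | 0 to 0.5 |

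The estimate is nearly the same at both horizons although the mean gain triples, because most pairs compare two weaned patients or two zeros.

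In the 30% v 30% row the estimate is exactly zero in about 62% of trials if days are counted whole, and in about 25% if they are not. Section 4.2 gives no rounding rule.

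**3. Precision of the VFD-90 mean difference.** With 30% zeros in both groups, the variance per group is about 0.3 × 0.7 × 88² = 1,626, so the standard error is √(2 × 1,626 / 47) = 8.3 days and the 95% CI is about ±16 days.

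**The case against.** The strongest reply is that Hodges-Lehmann legitimately targets the median pairwise difference and is the usual companion to the Mann-Whitney test. A value different from the mean difference is then a different target, not an error. This stands, and it is why the measure can stay for VFD under an accurate name.

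A reader might go further and infer that the results would hide the size of harm and benefit. The documents do not support that. Section 4.2 makes the reintubation rate a secondary outcome, and under Section 5.1 it gets an absolute difference with a bootstrap CI. Mortality at day 28 and day 90, respiratory status at both days and successful extubation status are also reported by group. Section 5.1 gives the mean and standard deviation per group, so only a CI for the mean difference is missing.

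A reader might also take a gap of 17 to 19 days against 1 or 2 as the expected distortion for VFD. That gap needs the day-90 horizon and an assumed 20-point difference in zeros. The protocol gives 30% overall, and Section 5.2.1.1 assumes the competing risk of death is identical in both groups. On those inputs the gap is about half a day to one day.

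Finally, the conflict with the p-value is not inevitable. At assumed reintubation rates of 20% v 10%, the Mann-Whitney test is significant in only about 25% of trials. None of this rescues 0 [0; 0] as a summary of the count when the test is significant.

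**Conclusion.** The point holds with limited impact. As written, Section 5.1 can put a zero-width interval at zero beside a significant p-value for number of reintubations. This happens across assumed rates from 5 v 14 to 12 v 24 of 47 patients, and the description as unbiased is wrong for outcomes of this shape.

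For VFD the weakness is one of sensitivity. The estimate is about 2 days where the mean gain is about 6 (day 28) or 19 (day 90) if zeros differ by 20 points, and the discrepancy is small if zeros are equal. The reintubation rates and the split of zeros are assumptions, because the protocol gives neither. The primary Cox analysis is unaffected, and other planned outcomes show the size of harm and benefit.

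**What to change.** In Section 5.1:

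- Delete *unbiased* and describe the Hodges-Lehmann estimate as the median of the pairwise between-group differences.
- For number of reintubations, replace it with the difference in mean number per patient and a bootstrap 95% CI.
- For VFD-28 and VFD-90, keep it and add the difference in means with a bootstrap 95% CI.

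The Mann-Whitney p-values can stay. The cost is a few sentences and a few lines of R, with no new data. The downside is two effect measures for VFD, one of them imprecise: about ±16 days for the VFD-90 mean difference with 30% zeros in both groups.
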